## Abstract

**Background:**

Many herbal medicines are traditionally used as anti-fatigue agents in east Asian countries; however, there is a dearth of clinical evidence supporting the anti-fatigue effects of such medicines and their mechanisms. This study is a feasibility trial to assess the clinical efficacy of *Gongjin*-*dan* (GJD) and verify its mechanisms by exploring fatigue outcomes, including endocrine and immunological biomarkers in humans.

**Methods/Design:**

To investigate the anti-fatigue effects of GJD and the mechanism underlying these effects, a randomised, double-blind, placebo-controlled crossover clinical trial was designed. Participants (24 healthy male volunteers) will be hospitalised for 4 days (3 nights), during which acute fatigue and stress conditions will be induced by sleep deprivation, and GJD or a placebo will be administered (twice daily). The primary outcome will be changes in serum cortisol levels, measured in the morning, as an objective biomarker of sleep deprivation-induced fatigue and stress. The secondary outcomes will include: the Fatigue Severity Scale; the Brief Fatigue Inventory, and the Leeds Sleep Evaluation Questionnaire scores; levels of salivary cortisol, epinephrine, norepinephrine, oxidative stress-related biomarkers, homocysteine, and immunological factors; and heart rate variability. After a washout period of more than 4 weeks, a second treatment phase will commence in which participants who were previously administered the placebo will receive the drug and vice versa, following the same treatment regime as in the first phase.

**Discussion:**

This study protocol provides a unique opportunity to enhance our understanding of fatigue and the effects of GJD on fatigue in terms of endocrine and immunological mechanisms by validating the study design and determining feasibility. Findings from this trial will help researchers to design a pilot or definitive clinical trial of traditional herbal medicine for chronic fatigue.

**Trial registration:**

Korean National Clinical Trial Registry CRIS; KCT0001681, registered on 29 October 2015.

## Background

Fatigue is a subjective symptom of lethargy experienced during or after performing daily work, or a feeling of a lack of energy sufficient to affect daily life. The average worldwide incidence of chronic fatigue is 11.1 % and most fatigue resolves with rest; however, treatment is required when fatigue is prolonged and reduces the quality of life of individuals and their families, or generally affects society [1, 2]. Among people with chronic fatigue, labor force productivity is known to decrease by 54 % and the cost of lost productivity is estimated to be $9.1 billion annually in the US. [3].

Fatigue is a multifactorial condition and the pathophysiological mechanisms of idiopathic chronic fatigue or chronic fatigue syndrome are unclear. For this reason, there is no standard treatment for chronic fatigue [4] and some patients with chronic fatigue, therefore, turn to complementary and alternative medicine (CAM) for treatment [5, 6]. In East Asian countries, CAM in the form of traditional herbal medicine is widely used to treat fatigue [7, 8]; the traditional herbal drug, *Gongjin*-*dan* (GJD), is generally prescribed by Korean traditional medicine physicians to treat patients with chronic fatigue in Korean traditional medicine clinics. Although the anti-fatigue effects of herbal medicines, including GJD [9], deer antler extract [10], and *tao*-*hong*-*si*-*we*-*tang* [11], have been demonstrated in animal studies, few clinical studies have focussed on these treatments. To encourage evidence-based practices in the traditional medicine field, well-designed studies must be conducted to evaluate the effects and mechanisms of action of traditional herbal medicines, including traditional anti-fatigue medicines.

This study is a feasibility trial to assess the clinical efficacy of GJD and verify its mechanisms by exploring fatigue outcomes, including endocrine and immunological biomarkers. The unique protocol described herein is designed to minimise confounding factors and other possible bias, and comprises a randomised, double-blinded, placebo-controlled crossover clinical trial with hospitalised subjects. However, the findings from this trial cannot be generalised to individuals suffering with chronic fatigue syndrome because sleep-deprived healthy men aged 19–45 years were chosen as the participants of this study to avoid confounding factors and improve internal validity.

This study design may serve as a guide for researchers seeking to effectively evaluate the effects and underlying mechanisms of traditional herbal anti-fatigue medicines as well as conventional drugs.

## Methods

### Objective

The aim of this study was to develop a protocol to (1) evaluate the anti-fatigue effects of GJD in acute fatigue; (2) verify the mechanisms underlying the observed effects by assessing changes in stress hormones, oxidative stress-related biomarkers, homocysteine, and immunological factors; and (3) clinically assess the effectiveness and safety of GJD in treating acute fatigue using the Korean version of the Fatigue Severity Scale (FSS-K), Brief Fatigue Inventory (BFI-K), and Leeds Sleep Evaluation Questionnaire (KMLSEQ) scores as well as carrying out daily fatigue and sleep evaluations and assessments of heart rate variability (HRV) and adverse events.

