The primary outcome analysis (*Δ = D*_*GJD*_*– D*_*PL*_) will be performed in two stages. First, a linear mixed effect model will be applied to assess the effect of treatment, sequence, and period with the random effect for subjects. The carryover effect due to preceding the treatment stage will then be estimated by testing the effect of sequence in the model. The linear mixed model will be modified by confounding the sequence effect to the error term if the carryover effect is not significant. Otherwise, the model will be rebuilt based on data collected in the first phase of the study. An analysis of variance (ANOVA) table for the model will be provided and least square means and their standard errors (95 % confidence intervals) will be reported for each treatment. Second, if the structure of data is balanced and the carryover effect is invalid, simple paired two-sample *t* tests or Mann Whitney *U* tests will be performed to evaluate the effect of GJD. The results will be shown as means and standard deviations for each treatment group and mean differences between the two treatments (95 % confidence interval) will be reported.

The analysis of secondary outcomes will be focussed on changes of measures within each treatment group from the baseline to the end of study. Again, the linear mixed effect model will be applied. The level of significance will be set to 0.05 (two-tailed) and all analyses will be performed with PROC MIXED and PROC GLM in SAS software, version 9.4 (SAS Institute Inc., Cary, NC, USA).

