## Discussion

Deciding on the appropriate primary outcome of a trial is one of the challenges of trial design. The primary outcome in this study protocol is serum cortisol level measured at 30 min after waking. Cortisol is closely related to fatigue and blunted cortisol levels are primarily observed in patients with fatigue [25–27]. Although fatigue is a subjective symptom, cortisol levels were selected as the primary variable over the questionnaire-derived results.

Cortisol should be measured at the same time every day due to circadian rhythm. Cortisol levels may, moreover, be affected by dietary supplements [28], caffeine [29], and intensive exercise [30], as well as foods with a high sugar, fat, or protein content [12, 13]. The crossover method and participant hospitalisation were implemented in this study to minimise confounding factors and other possible bias [31].

To determine perceived symptoms and to compare these with objective outcomes, the results of self-reported questionnaires including the FSS-K, BFI-K, KMLSEQ, and daily fatigue and sleep evaluation questionnaires will be evaluated.

Epinephrine, norepinephrine, and HRV are related to the autonomic nervous system and as such are stimulated as a response to stress in the human body. Most individuals experiencing fatigue have hyperactive sympathetic nerves and hypoactive parasympathetic nerves [32, 33], and variations in autonomic nerve activity in the fatigue state can be observed as changes in serum concentrations of epinephrine and norepinephrine as well as in HRV [34].

In comparisons of normal individuals to those experiencing fatigue, it has been reported that circulating oxidative stress increases with fatigue, but that antioxidant levels decrease [35–37]. Immunity disturbances have been researched for potential involvement in chronic fatigue syndrome and analysis of immunological factors are, therefore, also included in this study [38, 39].

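### The aim to verify mechanisms rests on marker changes alone: a comparison with perceived fatigue is intended but has no stated analysis, and 24 men could show only a strong link

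*Protocol article*

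**What the plan says.** The Objective section lists three aims. The second is to "verify the mechanisms underlying the observed effects by assessing changes in stress hormones, oxidative stress-related biomarkers, homocysteine, and immunological factors", so it states both a claim (verification) and a means (marker change). The Background uses the same verb: "This study is a feasibility trial to assess the clinical efficacy of GJD and verify its mechanisms by exploring fatigue outcomes". The Abstract repeats this.

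For the primary outcome, the Statistical analysis section says that "a linear mixed effect model will be applied to assess the effect of treatment, sequence, and period with the random effect for subjects". For all secondary outcomes, which include both the markers and the fatigue questionnaires, it says "The analysis of secondary outcomes will be focussed on changes of measures within each treatment group from the baseline to the end of study", followed by "Again, the linear mixed effect model will be applied".

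The Discussion gives the purpose of the questionnaires as "To determine perceived symptoms and to compare these with objective outcomes". It names no marker, score, time point or method for that comparison.

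Serum cortisol appears in two roles. The Abstract uses it as the primary outcome, "as an objective biomarker of sleep deprivation-induced fatigue and stress", and the footnote to Table 1 lists it among the stress hormones.

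**The concern.** A model for one marker answers whether that marker changes, or differs between treatments. To say that the marker underlies a fatigue effect, the marker and the fatigue measure have to be related to each other, and no stated analysis does that. Correcting for multiplicity would not help, because each corrected test would still address one marker in isolation.

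Two features of the plan make this sharper.

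- **Within-treatment focus.** The Treatment and evaluation phase section restricts sleep in both periods. A change from baseline under GJD may therefore be the effect of sleep loss. Only the contrast with placebo separates the two.
- **Cortisol's two roles.** The same cortisol shift could be counted as the anti-fatigue effect (first aim) and as its mechanism (second aim).

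At stake is the second objective: carried out as written, the analysis cannot meet it. The crossover does yield, for each man, a GJD-minus-placebo difference in both marker and fatigue score, so a within-man analysis is possible from data already planned.

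**Working it through.** **1. Objective against analysis.** The objective promises verification of what underlies the effects, by marker change. The effects named for the mixed model are treatment, sequence, period and subject. The text names no correlation, no regression of fatigue change on marker change, and no mediation step. The mixed model has a treatment term, so a GJD-versus-placebo contrast for each marker is available, but the stated focus is change within treatment.

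**2. What a marker test shows when there is no link (illustration).** The shift and the distributions are assumptions, not figures from the article. Take 24 paired GJD-minus-placebo differences, a marker shift of 0.8 SD, a fatigue shift of 0, a true correlation of 0, normal data and two-sided 0.05. In 20,000 simulated trials:

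| Result | Share of trials |
|---|---|
| Marker test significant | 96% |
| Fatigue test significant | 5% |
| Marker significant, fatigue not | 92% |
| Correlation significant (absolute r above 0.404) | 5% |

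A noncentral t calculation with 22 degrees of freedom also gives 96% for the marker test. So even the better, between-treatment marker test is almost always positive here, although the marker has nothing to do with fatigue.

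**3. What 24 men could show if a link were analysed.** The sample size of 24 (2 × 12) comes from a pilot-study rule in the Sample size section. There is no power calculation to reproduce. The correlations below are assumed. Fisher's transformation gives z = atanh(r), with SE = 1/√(24 − 3) = 1/√21 = 0.218.

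- 95% CI for an observed r of 0: tanh(±1.96 × 0.218) = −0.40 to 0.40.
- 95% CI for an observed r of 0.40: atanh(0.40) = 0.424; 0.424 ± 0.428 gives −0.004 to 0.851; back-transformed, 0.00 to 0.69.
- Power = Φ(atanh(r) × √21 − 1.96):

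| True r | Power |
|---|---|
| 0.3 | 29% |
| 0.4 | 49% |
| 0.5 | 71% |
| 0.6 | 89% |

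- True r for 80% power: tanh((1.96 + 0.84)/√21) = tanh(0.611) = 0.545.
- With sequence in the model, one more degree of freedom is used: tanh(2.80/√20) = tanh(0.626) = 0.56. The picture does not change.

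**4. Timing of the pairs.** Blood is drawn at 06:30, and questionnaires are completed at 18:30–21:00. The Secondary outcome section says the BFI asks about the present and the past 24 h, so the day 4 evening BFI-K covers the day 4 draw. For the baseline, serum cortisol is taken on day 2. The running text does not say which evening's BFI-K is its counterpart, so that pairing has to be fixed.

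**The case against.** The strongest reply has four parts.

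- **It is only missing detail.** This is a condensed article, and an exploratory association could sit in the full protocol or the SAP. A focus on change does not exclude other analyses. This stands as far as the method goes: the absence of a correlation from the article would be no fault alone. It does not answer the mismatch, because the objective itself names marker change as the means of verification.
- **A comparison is intended.** This stands. A reader might infer that the trial plans nothing to connect markers with perceived fatigue. The Discussion says otherwise, and what is lacking is any stated analysis.
- **No false claim is announced.** This stands too. A reader might infer that any marker shift will be reported as a verified mechanism. The article contains no such rule. It calls itself a feasibility trial, says it is not powered for effectiveness, and looks to further studies. The wording permits that reading but does not prescribe it. The same modesty makes *verify* harder to defend.
- **Objective and analysis agree, and the observed effects may mean cortisol.** If so, cortisol would be both the effect and a candidate mechanism, and the other markers would still not be related to it.

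A reader might also see the gap between morning blood and evening questionnaires as a defect. The 24-hour recall of the BFI answers that for day 4.

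**Conclusion.** The concern holds as a mismatch between a stated aim and the analysis that is meant to serve it. The plan can show that a marker moves, and through the treatment term that it moves differently under GJD. It cannot show that the marker underlies an effect on fatigue. With all 24 men contributing a pair of differences, only a strong link (a true correlation of about 0.55) would be detected with 80% power; moderate links of 0.3 to 0.4 would be missed half the time or more. These figures assume complete data, approximate bivariate normality and a two-sided level of 0.05. Dropout would worsen them.

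The point is worth correcting but limited. No figure in the article is shown to be wrong, and the primary comparison of cortisol change does not depend on it.

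**What to change.** 1. In the Abstract, Background and Objective, replace *verify* with *explore* where mechanisms are concerned.
2. In the Statistical analysis section, base conclusions about markers on the GJD-versus-placebo difference in change, and keep within-treatment change as description.
3. Give the Discussion's intended comparison a method. For serum cortisol and a short list of markers, regress each man's GJD-minus-placebo difference in BFI-K change on his difference in marker change, with sequence in the model to absorb the period effect. Report the slope and correlation with 95% CI, labelled exploratory. Name the list in advance: besides serum cortisol there are 20 blood markers to choose from (2 catecholamines, 9 oxidative stress-related, homocysteine, 5 cytokines, 3 cell types).
4. Fix beforehand which BFI-K assessment is paired with the baseline draw and which with the day 4 draw.
5. State that the association does not establish mediation. Other causes can move both measures, and a true mediator that acts alike in every man may show little correlation. For that reason, and because power is low, a detected association should not be a condition for calling a result consistent with a mechanism.

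The cost is changed wording and a few regressions on data already planned. The downside is a weaker claim and some imprecise estimates.

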### Design and setting

This randomised, double-blind (both patient and practitioner or assessor), placebo-controlled crossover clinical trial will be conducted in Republic of Korea.

#### Recruitment period

Participant recruitment began in September 2015 at the Daejeon Korean Medicine Hospital of Daejeon University, and it is expected to be completed in December 2015.

#### Methods of recruitment

Twenty-four participants will be recruited for this trial, and participants will be recruited using online and printed advertisement of the study. Advertisements will be posted on the online bulletin board of the Daejeon Korean Medicine Hospital of Daejeon University, and printed advertisements will be posted in stores in university towns and on school bulletin boards. Advertisements will also be posted on online social networking platforms. The relevant trial information will be conveyed to the potential participants prior to their first visit to the hospital.

#### Study plan

Subject information will be collected after oral and written consent is obtained from each participant at the first visit.

##### Screening phase

After potential participants voluntarily consent to the study, they will be screened using pre-determined inclusion/exclusion criteria at the first visit. The participants will be instructed to sleep for at least 7 h daily for 1 week before admission and to avoid new medications, alcohol, and caffeine consumption for 2 days before admission. Participants will be randomly allocated to one of two groups. The group allocation will be concealed from both the participants and the practitioners.

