**Fig. 1 Fig1:**
[figure not shown]
Flowchart describing the study plan

Blood samples will be collected at 06:30 for analysis of serum cortisol, stress hormones, oxidative stress-related biomarkers, homocysteine, and immunological factors. Saliva samples will be collected at 06:30, 12:00, and 21:00 for analysis of salivary cortisol, while HRV will be assessed at 15:00–17:00. Self-reporting of FSS-K, BFI-K, KMLSEQ, and daily fatigue and sleep status will be carried out via questionnaires after dinner on days 1, 2, 3, and 4.

After a 4-week washout period, participants will be admitted to phase II for 4 days, during which they will undergo the same schedule.

The schedule of events for the trial is outlined in Table 1 and the study participants’ timeline of activities, treatments, and assessments during hospitalisation is shown in Fig. 2.

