### Study participants

#### Inclusion criteria

Participants are eligible for inclusion in the study if they meet the following criteria:Healthy male volunteers aged 19 to 45 years at the screening visitParticipants must weigh over 45 kg, with a body mass index of 18.5–30 kg/m^2^ at the screening visitParticipants must not have any congenital defects or chronic diseases that have been present within the 3 years prior to the screening visit and should have no pathological or abnormal clinical findings on physical examinationParticipants must not have any sleep disorders and must have Pittsburgh Sleep Quality Index (Korean version; PSQI-K) scores of 5 points or lowerParticipant must keep normal nocturnal sleeping hours (between 21:00 and 09:00) for a week before the first administration of the investigational drug (or placebo)Participants must sleep at least 7 h per night for a week before the first administration of the investigational drug (or placebo)Participants must be nonsmokers or ex-smokers who stopped smoking at least 1 year before the screening visitParticipants must comprehend the purpose and process of the study as well as the properties of the investigational drug and must voluntarily sign a written informed consent approved by the Institutional Review Board of Daejeon Korean Medicine Hospital of Daejeon University

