#### Exclusion criteria

Participants who experience, have, or have had one or more of the following will be excluded:A clinically significant medical history or a current disease in one of the following areas: cardiovascular, respiratory, gastrointestinal, hepatic, metabolic and endocrine, renal and urinary, reproductive, musculoskeletal, skin and connective tissue, neurological, psychiatric, or allergic (other than seasonal allergies that are asymptomatic at the screening visit) diseaseA medical history of gastrointestinal diseases (oesophageal achalasia, oesophageal stricture, or Crohn’s disease) or operations (other than simple appendectomy or hernia surgeries) that may affect drug absorptionLaboratory test results showing alanine aminotransferase (ALT) or aspartate aminotransferase (AST) levels of more than twice the upper limit of the normal rangeA history of alcohol or drug abuse within the 12 months before the screening visitHistory of regular alcohol consumption (>210 g/week) within the 6 months before the screening visit. (Beer (5 % v/v): 250 mL = 10 g, *soju* (20 % v/v): 50 mL = 8 g, wine (12 % v/v): 125 mL = 12 g)Participation in another clinical study during the 2 months before the screening visitTreatment with drugs with known effects on drug-metabolising enzymes (e.g. dexamethasone, phenytoin, carbamazepine, rifabutin, rifampicin, phenobarbital, ketoconazole, itraconazole, clarithromycin, atazanavir, indinavir, nelfinavir, ritonavir, clarithromycin, telithromycin, voriconazole, etc.) during the 30 days before the screening visitWhole blood donation during the 2 months before the screening visit, or specific blood component donation in the month before the screening visitSeated systolic blood pressure ≥140 mmHg or diastolic blood pressure ≥90 mmHg at the screening visit Intake of prescribed or over-the-counter drugs during the 7 days before the first administration of the investigational drug (or placebo) Consumption of alcohol during the 7 days before the first administration of the investigational drug (or placebo) Serious, acute, or chronic medical or mental conditions or abnormal laboratory findings that may be exacerbated by administration of the investigational drug or participation in the study, or that may affect the study outcomes Hypersensitivity to the investigational drug or any of its components Absence of intention or ability to adhere to the behavioural rules and requirements as specified in the present protocol Any person considered unsuitable for participation in the study by the principal investigator

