
### Intervention

Trial medications will be prepared by Kyoung-Bang Pharmaceutical Co. Ltd. (Incheon, Republic of Korea) certified in Good Manufacturing Practices of herbal medicine extract pills and granules from the Ministry of Food and Drug Safety (MFDS). Quality control and quality assurance on the quality and safety testing, the packaging, and the contents of the treatment interventions including checks for potential contaminants, such as heavy metals or steroids, will be undertaken by the manufacturers to ensure treatment drug stability and quality.

Quality control and quality assurance regarding the identification of products as well as quality and safety testing will be conducted by the manufacturer. The raw herbs will be washed, dried, ground, and mixed with a pure form of honey (*Mel*) before being wrapped in gold foil and formed into pills. The pills will be packaged in identically shaped containers weighing 3.75 g each. The GJD and placebo pills will be formulated to a similar size, shape, taste, and flavour and will be wrapped in gold foil.

GJD consists of three medicinal herbs (*Ginseng radix*, Korean angelica, *Corni fructus*), two animal-derived materials (*Cornus cervi parvum* and *Moschus*) and *Mel*. All constituents of the formulation will comply with *Korean Pharmacopoeia* standards [40]. A placebo will be manufactured by the same pharmaceutical company and will be comprised of corn starch as the main ingredient, as well as small amounts of *Dioscoreae rhizoma*, *Poria sclerotium*, *Mel*, a colouring agent, and a flavouring agent. Each pill will weigh 3.75 g and the amounts and sources of each component of the formulation are shown in Table 2. The participants will take GJD or placebo twice a day 30 min before breakfast and dinner, a total of six times during hospitalisation.

**Table 2 Tab2:** Composition of *Gongjin-dan*

Herbal name		Scientific name (local name)	Quantity (g/pill)	Place of origin
Herbs	*Corni fructus*	*Cornus officinalis* Siebold et Zucc. (山茱萸)	0.9	Korea
	Korean angelica	*Angelica gigas* Nakai (當歸)	0.9	Korea
	*Ginseng radix*	*Panax ginseng* C.A. Meyer (人蔘)	0.9	Korea
Animal derives	*Moschus*	*Moschus moschiferus* L. (麝香)	0.15	Russia
	*Cornus cervi parvum*	*Cervus nippon* Temminck (鹿茸)	0.9	Russia
Diluting agents	*Mel*	*Apis indica* Radoszkowski (蜂蜜)		Korea
	*Aurum*	Gold (金)		Korea

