#### Primary outcome

The primary outcome of this study is the participants’ serum cortisol levels. The effect of GJD on serum cortisol will be assessed by observing differences in cortisol levels before (day 2) and after (day 4) administration with GJD or placebo dosing after fatigue has been induced by sleep deprivation in healthy subjects. Considering circadian rhythms, cortisol will be measured at a specific time daily. Serum cortisol levels will be measured on an empty stomach 30 min after waking, and subjects will not eat foods that might affect cortisol levels, such as those high in sugar, fat, or protein for 12 h before the first administration of the investigational drug or placebo [12, 13].

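### The pre-admission instruction on drugs and alcohol covers 2 days, but the exclusion criteria cover 7

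*Protocol article*

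**What the plan says.** The Screening phase section of the protocol article gives participants two behavioural instructions in one sentence. On sleep, they are "instructed to sleep for at least 7 h daily for 1 week before admission". On intake, they are to "avoid new medications, alcohol, and caffeine consumption for 2 days before admission".

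The Exclusion criteria section sets a different window for two of these items. It excludes men for "Consumption of alcohol during the 7 days before the first administration of the investigational drug (or placebo", and likewise for "Intake of prescribed or over-the-counter drugs during the 7 days before the first administration of the investigational drug (or placebo". Caffeine does not appear among the exclusion criteria.

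For sleep, the matching inclusion criterion asks men to "sleep at least 7 h per night for a week before the first administration of the investigational drug", so instruction and criterion both run for a week.

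**The concern.** The same behaviours carry two different windows. For alcohol the instruction is shorter than the criterion. For drugs it is shorter and also narrower, because it speaks of new medications where the criterion covers any prescribed or over-the-counter product.

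Most of the time-limited exclusions look back from the screening visit and can be checked there. These two look back from the first dose. Any of their days that fall after screening cannot be verified at that visit, so compliance depends on what the men are told to do. The only drug and alcohol instruction in the article says 2 days.

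A man who drinks on, say, the 4th day before admission has done as instructed, yet he is ineligible or a protocol deviation. The Screening phase section describes allocation straight after the instructions, so this could come to light after randomisation. With 24 participants, one man is 1/24, about 4% of the sample.

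**Working it through.** The plan gives no figure to reproduce, so the check is a comparison of the two texts and a count of days.

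**Comparison**

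| Item | Instruction (Screening phase) | Eligibility criterion | Agreement |
|---|---|---|---|
| Sleep of at least 7 h | 1 week before admission | 1 week before first dose | Same length, slightly different anchor |
| Alcohol | 2 days before admission | 7 days before first dose | Instruction shorter |
| Drugs | 2 days before admission, new medications only | 7 days before first dose, any prescribed or over-the-counter drug | Instruction shorter and narrower |
| Caffeine | 2 days before admission | None | No conflict |

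**When is the first dose?** The instruction counts back from admission and the criteria count back from the first dose, so the gap depends on the day of that dose. The schedule table and timeline figure are not available, but three statements bear on it:

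- Intervention: the pill is taken "twice a day 30 min before breakfast and dinner, a total of six times during hospitalisation".
- Treatment and evaluation phase: "Blood samples will be collected at 06:30 for analysis of serum cortisol".
- Primary outcome: cortisol is compared "before (day 2) and after (day 4) administration with GJD or placebo dosing".

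If the 06:30 sample on day 2 is taken before dosing, the possible starts are:

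- Before breakfast on day 2: 2 + 2 + 2 = 6 doses by day 4, which agrees with the stated total.
- Before dinner on day 2: 1 + 2 + 2 = 5 doses, one short.

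So a start before breakfast on day 2 fits. A start on day 1 can also give six doses (for example before dinner: 1 + 2 + 2 + 1 = 6), but day 2 would then not be before administration. It is kept as the alternative.

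**Days left uncovered** = days in the 7-day window before admission, minus the 2 days in the instruction.

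- First dose on the morning of day 2: the window is hospital day 1 plus the 6 days before admission. Uncovered: 6 − 2 = 4 days (the 3rd to 6th before admission), that is 4 of 7.
- First dose on day 1: the window is the 7 days before admission. Uncovered: 7 − 2 = 5 days (the 3rd to 7th before admission), that is 5 of 7.

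If the instruction is set to 7 days before the first dose, the gap is 0 on either reading.

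**The case against.** The strongest reply is that nothing here is a true contradiction. One text is a behavioural instruction and the other an eligibility rule; both are met by following the stricter one, and the instruction does not permit drinking or drug use on the earlier days. That is correct as logic. It does not help the man who is given the instruction and relies on it.

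A second reply is that men may learn the 7-day rule elsewhere. The Methods of recruitment section says trial information is given before the first visit, and there is oral and written consent. The Screening phase section also omits other rules, such as the permitted sleeping hours and the 12-hour food restriction, which must reach participants by another route. This stands as a real possibility, and it limits what can be said about how often the problem would occur. It does not remove the mismatch: the issue is two different stated windows for the same behaviours, not a detail left out of a condensed article.

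Two smaller points also stand in part. The sleep instruction and its criterion have different anchors (admission against first dose), so their match is in length only; the difference is immaterial here. The contrast between new medications and any drug matters less than the length of the window, because men with significant or chronic disease are excluded and continuing medication can largely be caught at screening.

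Finally, no effect on validity, power or interpretation has been shown. That is accepted, and none is claimed.

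**Conclusion.** The concern holds as a minor inconsistency between an instruction and the eligibility criteria. A participant who obeys the only stated drug and alcohol instruction can still meet an exclusion criterion on 4 of the 7 excluded days, or on 5 of 7 if dosing starts on day 1.

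The count of 4 rests on inferring a first dose before breakfast on day 2. That a gap exists does not depend on this inference. The count concerns the first admission, since the criteria are tied to the first administration.

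The text mismatch is certain. The operational harm is only possible, and its frequency is unknown. At worst it means a few avoidable late exclusions or deviations. The full analysis set remains the main analysis and the per-protocol set a sensitivity analysis, so the main result is not called into question.

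**What to change.** In the Screening phase section, and in whatever participants are given, replace the drug and alcohol part of the instruction with: no prescribed or over-the-counter drugs and no alcohol for 7 days before the first dose. Keep the 2-day rule for caffeine, which no eligibility criterion restricts.

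The cost is one revised participant instruction and perhaps slightly slower recruitment. The design, sample size and analysis stay as they are.
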